**Figure 4 figure4:**
[figure not shown]
The WWJ application’s main user interface. WWJ: Walking With Just-in-Time Adaptive Intervention.

### Measures and Materials

#### Apple iPhone and Watch Device Compatibility and Software

To ensure compatibility with the WWJ application, participants will use an iPhone 6s or newer running iOS 13 or later and an AW Series 3 or newer running watchOS 8.0 or later. If the participant does not own an AW Series 3 or is newer, they will sync a borrowed AW Series 3 running watchOS 8.0 or later with their iPhone. All applicable updates will be conducted for optimal performance. We will monitor iOS and watchOS updates to identify any potential impacts on just-in-time and JITAI notifications and address any issues that arise.

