### Objective, Aims, and Research Questions

This protocol paper presents the development of the “Walking With Just-in-Time Adaptive Interventions” (WWJ) iPhone and AW app, server, and methodology for a 6-week pilot study among adults who are not meeting the 2020 WHO PA recommendations. The primary aims of the WWJ’s study are to examine the feasibility and initial impact of a 2-week JITAI approach for increasing walking behavior (ie, walking speed, distance, and duration) and decreasing stationary behavior (ie, duration of SB and idle standing) compared to a 2-week baseline observation period and a 2-week just-in-time learning period. Thus, our corresponding research questions include: (1) Is the WWJ feasible, regarding recruitment, retention, intervention fidelity, acceptability, adherence, and engagement? (2) To what extent does the just-in-time approach impact walking and stationary behavior compared to baseline? (3) How do changes in walking and stationary behaviors across a 2-week just-in-time and a 2-week JITAI approach compare to baseline?

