## Methods

### Overview of Study Design

This pilot feasibility study will use a 1-way within-subjects repeated-measures design to examine changes in walking and stationary behaviors across the 3 time periods: baseline, just-in-time, and JITAI. This study will consist of a preintervention measurement session, followed by a 2-week observation period that will serve as a baseline for walking and stationary behaviors, a 2-week just-in-time learning period, a 2-week JITAI period, and concluding with a postintervention measurement session (Figure 1). The receptiveness-in-context data from the just-in-time learning period will be used to train and individually adapt the JITAI server by learning the ideal contexts in which the participants are most receptive to each of the 3 intervention notifications, as detailed in the Architecture of the WWJ App and Server section.

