### Architecture of the WWJ App and Server

The research team has previously detailed a comparable server and application development [19]. The WWJ fully automated multiagent system operated on a per-agent architecture comprising 4 modules—context analyzer, learner, executor, and communicator (Figure 2). In the WWJ agent-level design, learning the support need policy is framed as a fully supervised classification problem rather than as a Markov Decision Problem [31] to account for the time constraints of a 2-week baseline and 2-week just-in-time learning period and the AW’s battery-life constraints, which are particularly so when leveraging the HR sensor and GPS networks. Architecture development began in spring 2021 and concluded in fall 2022. Aligning with the CONSORT EHEALTH checklist (V.1.6.1), all updates to the WWJ application and server after this finalized development will be identified by date, version number, and description to allow for the replicability of the intervention [32].

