##### Walking and Stationary Behaviors

Our WWJ app will collect timestamped walking and stationary behaviors once respective thresholds are met (described previously in the Architecture of the WWJ App and Server section). The Apple watchOS behavior detection APIs use its combined location sensors—the GPS, the Globalnaya Navigatsionnaya Sputnikovaya Sistema, Galileo, and Quasi-Zenith Satellite System—and its motion sensors—triaxial accelerometer and gyroscope—to detect walking and stationary behaviors via Apple’s proprietary algorithms. These walking behaviors will include duration to the nearest whole second, distance to the nearest meter, and speed calculated from the collected distance divided by duration to the nearest meter per second. In addition, when a walking bout is detected, HR will be collected every 10 seconds. The duration of stationary behavior will be recorded to the nearest whole second.

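### Operating-system updates may reach participants between study periods and are checked only for their effect on notifications, although the operating system also measures the outcomes

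*Protocol article*

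**What the plan says.** The device section of the Protocol article (Apple iPhone and Watch Device Compatibility and Software) gives version floors but no fixed version: "participants will use an iPhone 6s or newer running iOS 13 or later and an AW Series 3 or newer running watchOS 8.0 or later". It then says: "All applicable updates will be conducted for optimal performance". The timing of these updates is not given. The only stated surveillance is: "We will monitor iOS and watchOS updates to identify any potential impacts on just-in-time and JITAI notifications", with a promise to deal with problems found.

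Under Walking and Stationary Behaviors, the watchOS interfaces use location and motion sensors "to detect walking and stationary behaviors via Apple’s proprietary algorithms". Distance and duration come from this detection, and speed is calculated from them.

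The design is a "1-way within-subjects repeated-measures design to examine changes in walking and stationary behaviors across the 3 time periods: baseline, just-in-time, and JITAI". There is one group and one order of periods.

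Version tracking is promised under Architecture of the WWJ App and Server, for the study's own software: "all updates to the WWJ application and server after this finalized development will be identified by date, version number, and description". No matching statement is made for iOS or watchOS.

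**The concern.** A comparison of each person with their own baseline needs the same measuring instrument in all three periods. Here part of the instrument is operating-system code that the study team does not control, and the stated rule is to update it. The team foresaw that updates could disturb the study, but the check it names concerns notifications in the just-in-time and JITAI periods. The observation period sends none, so that check says nothing about the baseline to which everything is compared.

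An update always affects a participant's later data, never the earlier data. With a fixed order and no concurrent control, a detection change in a consistent direction would be confounded with period. Staggered enrollment would dilute it but not reverse it.

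There is a second route. Walking notifications are labeled successful by comparing just-in-time behavior with observation-period behavior in the same contexts. A detector change between those periods could mislabel the data that train the participant's walking policies.

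Strengths and Limitations says that the pilot's effect sizes will inform the sample size of a future randomized trial, so an artifact could carry forward.

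**Working it through.** **Does another provision cover the gap?**
- Data Processing screens for gross artifacts: overlapping timestamps, bouts under 10 seconds, walking over 5 hours, speeds above 3 m/s. A modest systematic shift would pass.
- The Analytic Plan mentions software only as a possible correlate of missing observations. A shifted value is not a missing one.
- The covariates foreseen there are demographic. Software version is not among them.

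**The plan's own figure.** Inputs from Sample Size and Power Estimates: m = 3 measurements, within-subject correlation ρ = 0.5, α = 0.05, f = 0.32, power 0.8, n = 17, 15% attrition. The noncentrality is λ = n·m·f²/(1−ρ), with df₁ = m−1 and df₂ = (n−1)(m−1). For n = 17, λ = 17 × 3 × 0.1024/0.5 = 10.44 and power is 0.794. For n = 18, power is 0.820. The stated 17 is reproduced to within rounding of the power, and 17/0.85 = 20. This confirms the test used below; the sample size is not at issue.

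**Effect of a detector shift.** The documents give neither the share p of participants updated between or within periods nor the shift d. Both are assumptions, with d in units of the between-participant SD of a period average. Every update is taken to shift detection by the same amount in the same direction.

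The expected false difference, JITAI minus baseline, is:
- Update at a period boundary: p·d. Example: 0.5 × 0.5 = 0.25 SD.
- Update at a uniformly random time in the six weeks: on average 1/6 of baseline and 5/6 of the JITAI period fall after the update, so p·d·(5/6 − 1/6) = (2/3)·p·d. Example: (2/3) × 0.5 × 0.5 = 0.17 SD.

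The planned ANOVA was simulated with the final sample of 18 (Results), ρ = 0.5, no true change, and 20,000 runs per scenario. Rejection rates at nominal 5%:

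| Timing | Share updated | d = 0.25 | d = 0.5 | d = 0.8 |
|---|---|---|---|---|
| Random | 25% | 5.4% | 5.7% | 7.0% |
| Random | 50% | 5.6% | 8.6% | 14.0% |
| Random | 100% | 8.6% | 20.3% | 44.6% |
| Boundary | 25% | 5.4–5.6% | 7.4–7.5% | 11.4–11.5% |
| Boundary | 50% | 7.9% | 15.7–16.2% | 33.4–33.7% |
| Boundary | 100% | 16.5–16.9% | 54.4–54.5% | 92.4–92.8% |

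Ranges in the boundary rows cover the two possible boundaries. With nobody updated, the rate stays near 5%.

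For scale, a shift d in every participant at one boundary corresponds to f = d·√2/3. It equals the planned f = 0.32 when d = 0.32 × 3/√2 = 0.68 SD.

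**The case against.** Several objections have force.

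- **A reader might infer that updates did shift the measurement.** The document does not support that. It says the algorithms are proprietary, not that any release changed them.
- **A reader might infer that updates were certainly installed during participation.** No timing is stated, and the sentence follows text on device compatibility and borrowed watches, so some updating may belong to set-up. Watching for effects on just-in-time and JITAI notifications makes later updating a fair inference, but no more.
- **Notifications depend on detection.** Walking prompts fire at 250 m from a detected start and stand-up prompts after 30 minutes of detected stillness. A marked detector change would alter prompting and might be noticed. A modest shift need not be, and baseline has no prompts.
- **The label problem is limited to walking.** Stationary success is the watch registering a minute of walking, with no comparison with the observation period.
- **The size cannot be put in minutes per day.** Applying a percentage to the roughly 8 hours of daily sedentary time in the Introduction would use a review figure for adults in general. This trial also counts idle standing and analyzes period averages.
- **An article may omit version logging that the full protocol contains.** That is possible, so the point rests on the update rule and check that are stated, not on missing logging.
- **The stated primary focus is feasibility and acceptability.** That limits the consequences, but the period comparison is also among the primary aims.

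**Conclusion.** The point holds in conditional form. The stated rule allows the outcome detector to change within a participant's six weeks, the stated check does not cover measurement, and the design could not separate a detection change from a period effect. Whether this occurred is unknown.

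Under the assumptions above, the consequence runs from negligible (about 5% when few update or the shift is small) to about 16% (half updated at a boundary, 0.5 SD). Higher rates require nearly everyone to be updated, larger shifts, or both, always in a common direction. That justifies an inexpensive safeguard and a cautious reading of the period differences, not a claim that the results are invalid.

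**What to change.** **Protocol text, for this document and the future trial.** In the device compatibility section, replace the general commitment to updating with a rule: update devices at the preintervention visit, then defer non-urgent iOS, watchOS and WWJ app updates until the postintervention visit, except updates needed for security or to restore function. Log the iOS and watchOS version and date for each participant. The cost is one set-up step and one logged field, and non-urgent updates are delayed by up to six weeks. Sample size is unaffected.

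**Data already collected.** Results states that collection was completed in 2024 and that the analyses are pending, so a new update rule cannot help this sample. Where versions can be recovered, identify participants whose operating-system version changed between periods and repeat the period comparisons without them as a sensitivity analysis. This costs one extra analysis, and precision will be low with 18 participants. If versions cannot be recovered, state possible detector change as a limitation of the period comparison and of the effect sizes carried into the future trial.

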#### Demographics

Demographics will be collected using an adapted survey based on the demographics section of the 2021 Centers for Disease Control and Prevention–approved Behavioral Risk Factor Surveillance System Survey Questionnaire [33] on the following items: age; sex; race and ethnicity; level of education; employment, marital, and student statuses; annual household income; current housing arrangement (ie, renting, owning, or in a dormitory); and current ZIP code.

#### Behavior Change Constructs

The stages and processes of PA change from TTM will be assessed using scales developed by Marcus et al [34]. Additionally, the 5-item Self-Efficacy for Physical Activity scale will assess an individual’s confidence in engaging in PAs despite barriers, such as tiredness, bad mood, time constraints, vacation time, and unfavorable weather conditions, that is, rain or snow [34]. PA self-regulation will be assessed using the 12-item version of the Physical Activity Self-Regulation scale, which has excellent internal consistency (Cronbach α=0.91) and good construct validity [35].

#### Anthropometrics and Resting Vital Signs

Body composition will be estimated using BMI (ie, body weight [in kg] divided by height [in m^2^]). Participants will remove their shoes and any excessive clothing for all measurements. Weight will be measured using a calibrated, portable Seca scale to the nearest 0.1 kg. Height will be measured using a calibrated, portable stadiometer to the nearest 0.5 cm. Using a standard stopwatch, radial resting HR will be measured for a full 60 seconds to the nearest beat after the participant is instructed to sit in a relaxed position in a chair with their back supported, feet on the floor, and arms supported at heart-level for 5 minutes in a private room [36]. Resting systolic and diastolic BP will be measured to the nearest mm Hg by a trained researcher using a standard portable BP machine (OMRON Intelli-Sense Series 7 Advanced Accuracy, Model BP760) and cuff size that allows for the bladder of the cuff to encircle at least 80% of the upper arm. The researcher will wrap the cuff firmly around the upper left arm of the participant at heart level and align the cuff correctly with the brachial artery. A second reading for resting HR and BP will be taken after an additional 1-2 minutes. If the BP readings are 5 or more mm Hg apart, a third reading will be obtained after a final 1-2 minutes of rest [36].

#### Contextual Variables

##### Busy Times of Day

During the baseline visit, participants will sync all their calendar systems (eg, Google, Microsoft Exchange, and Outlook.com) to their Apple Calendar on their paired iPhone. They will be instructed to use the Apple Calendar to schedule times they cannot be notified during by marking those events as “busy.” Participants will be advised not to mark large blocks of time (eg, a full 8-hour workday) as “busy” and to ensure all scheduled physically active times are marked as “free.”

##### Geographic Location

Participants will be instructed to provide a text label of their physical locations via the “tag” button on the WWJ user interface the first time they visit a new location while they are in that precise location (eg, tagging work while seated at one’s work desk). After pushing the “tag” button, participants will have the option of selecting home, work, school, gymnasium, park, and other; if the user selects “other,” they can type in any new text label (eg, “friend’s house” as illustrated in Figure 4). Instructions will be given not to tag: (1) a location in a parking lot, (2) a nonprecise or overly generic location (eg, university campus versus a specific university building), or (3) behavior they are participating in (eg, walking around the neighborhood). Once tagged, the AW system will register each instance when the participant is in this location with a 50-m accuracy whenever data are recorded.

##### Weather

The ClimaCell application programming interface (API) of watchOS (currently Tomorrow.io API; Tomorrow Companies Inc) will collect participant data on precipitation to the nearest inch, temperature to the nearest Celsius degree, humidity to the nearest percent, and wind speed to the nearest mile per hour at the participant’s current precise geographic location, leveraging detected latitudes and longitudes on the AW, with a 50-m accuracy during walking and stationary bouts.

##### Walking and Stationary Behaviors

Our WWJ app will collect timestamped walking and stationary behaviors once respective thresholds are met (described previously in the Architecture of the WWJ App and Server section). The Apple watchOS behavior detection APIs use its combined location sensors—the GPS, the Globalnaya Navigatsionnaya Sputnikovaya Sistema, Galileo, and Quasi-Zenith Satellite System—and its motion sensors—triaxial accelerometer and gyroscope—to detect walking and stationary behaviors via Apple’s proprietary algorithms. These walking behaviors will include duration to the nearest whole second, distance to the nearest meter, and speed calculated from the collected distance divided by duration to the nearest meter per second. In addition, when a walking bout is detected, HR will be collected every 10 seconds. The duration of stationary behavior will be recorded to the nearest whole second.

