Moreover, a 2018 review found that adults spend approximately 8 hours participating in sedentary behavior (SB) daily [7]. SB is characterized by EE less than or equal to 1.5 metabolic equivalents of task (MET), with the Sedentary Behavior Research Network further detailing in 2017 that SB occurs while in a seated, reclined, or lying posture [8]. Emerging evidence indicates that excessive SB participation is associated with an increased prevalence of cardiometabolic diseases and risk of all-cause mortality [9] while reducing SB participation and subsequently increasing PA participation—even to a light-intensity—can significantly improve BMI and diastolic and systolic blood pressure (BP) [10-12]. Additionally, while intermittent standing bouts may be a feasible approach to reduce prolonged sitting, reclining, or lying through a postural change, passive or “idle” standing produces limited bodily movement, typically remaining below the 1.5 MET threshold to classify as light-intensity physical activity (LPA) [13].

Thus, reducing stationary behavior (ie, SB and idle standing) is a public health challenge that should be addressed through movement behaviors that reach MET thresholds at or above an LPA level. While specific LPA guidelines have yet to be established, the WHO advises adults to minimize SB time and substitute that time with any type and intensity of PA, including LPA [5]. Given that walking is generally feasible and accessible for adults who ambulate [5,14], it can serve as an ideal mode for not only replacing stationary behavior with LPA participation but also meeting WHO MVPA recommendations [5,14,15]. Walking paces around 0.82-0.89 m/s can exceed the 1.5 MET threshold for LPA [16,17]. To achieve the MPA threshold, walking must be performed at faster paces, typically around 1.3-1.8 m/s [16]. Since the 2020 WHO recommendations recognize that every minute of MVPA—regardless of bout duration—contributes toward an individual’s weekly targets [5], promoting walking behavior at faster paces may be an appropriate approach to increasing weekly MVPA volume while also breaking up stationary behavior.

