### Analytic Plan, Sample Size, and Power Estimates

#### Data Processing

The WWJ server will store all data for manual processing. Data processing will start by ensuring all timestamps for walking and stationary bouts are sequentially aligned. This alignment will allow for accurate calculations for transitions between these states and other activity modes. Outliers, including device-specific artifacts, such as overlapping timestamps and erroneous bout durations such as those too short to be meaningful (eg, <10 seconds) or exceeding physical limits (eg, >5 hours of continuous walking) and walking speeds surpassing human capacities (eg, >3 m/s) [40], will be identified and reviewed for manual correction or exclusion. Additionally, geographic locations tagged in the data and any nonadherence responses marked as “other” and inputted by participants will be downloaded and coded using an inductive approach to group similar entries into cohesive categories emerging organically from the data. Once fully processed, all data will be stored in a standardized format.

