#### Analytic Plan

Using the latest version of JMP Statistical Software (currently JMP, version 19.01, SAS Institute Inc, 1989-2025), preliminary analyses will include baseline descriptive statistics and exploratory data analysis. Baseline characteristics of the participants (eg, self-reported MVPA minutes from the screener, demographics, behavior change constructs, anthropometrics, and resting vital signs); recruitment, enrollment, and retention rates; implementation fidelity; adherence and compliance rates; user-burden; acceptability; treatment-specific expectations of benefits and preferences will be summarized in frequency tables for categorical variables and means and SDs for quantitative variables. Qualitative responses to applicable feasibility notifications and open-ended exit surveys will be explored.

Walking behavior and stationary time measures through all 3 periods—baseline, just-in-time, and JITAI—support a 1-way within-subjects ANOVA analysis of continuous measures (eg, average bout duration, speed, distance, and stationary time per study period for each participant) to demonstrate the feasibility of effecting a change in the behavior profile throughout the WWJ study. The intended 1-way within-subjects ANOVA assumes limited outliers, normality, and sphericity, which will be assessed graphically using boxplots, the Shapiro-Wilk test, and Mauchly test, respectively. Outliers, if present, will be assessed for their potential to weaken the analysis and removed if necessary. Nonnormal data will be transformed using the Box-Cox procedure to achieve normality. If sphericity is violated, the Greenhouse-Geisser and Huynh-Feldt corrections will be used. Tukey post hoc testing will be used to explain the differences between WWJ periods. If normality cannot be approximately achieved, the nonparametric Friedman test will be used. The model will be extended to allow for covariates if data screening of other collected demographic measures (eg, education) suggests their importance.

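### Walking speed is stated to the nearest whole metre per second, too coarse for a behaviour in the primary aim; it should be analysed unrounded from the stored distance and duration

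*Protocol article*

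**What the plan says.** The section Walking and Stationary Behaviors sets the recorded resolution of each walking measure in one sentence. It begins "These walking behaviors will include duration to the nearest whole second, distance to the nearest meter" and ends with "speed calculated from the collected distance divided by duration to the nearest meter per second". The article gives no finer resolution for speed anywhere else.

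The Background section places the relevant paces on a much finer scale. For light intensity it says "Walking paces around 0.82-0.89 m/s can exceed the 1.5 MET threshold for LPA"; for moderate intensity, "walking must be performed at faster paces, typically around 1.3-1.8 m/s". Data Processing marks the upper end of plausible values: "walking speeds surpassing human capacities (eg, >3 m/s".

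Speed is not incidental. The aims include "increasing walking behavior (ie, walking speed, distance, and duration". The Analytic Plan treats speed as one of the "continuous measures (eg, average bout duration, speed, distance, and stationary time per study period for each participant". Its secondary analyses score whether prompts to walk faster or longer succeeded. Under Architecture of the WWJ App and Server, success of a walking prompt is judged by comparing current behaviour with the observation period in the same contexts, and these labels train each participant's policy.

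**The concern.** On a whole-metre-per-second scale, nearly all ordinary walking takes one of two values, 1 or 2. Most realistic gains in pace fall inside one value and disappear at bout level, while trivial changes across 1.5 m/s appear as a full unit. Three things are at stake:

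- the sensitivity of the speed comparison between baseline, just-in-time and JITAI periods;
- the size of the reported effect, which Strengths and Limitations says will inform the sample size of a future randomized trial;
- the meaning of a successful walk-faster prompt, if success is scored on the rounded value.

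**Working it through.** **The plan's own figure.** The sample size does not depend on this point, and it reproduces. For a one-way within-subjects ANOVA with m = 3, ρ = 0.5 and f = 0.32, the noncentrality is λ = f²·n·m/(1−ρ) on 2 and 2(n−1) degrees of freedom. At n = 17 and α = 0.05, power is 0.794, close to the stated 0.8. Then 17/0.85 = 20.

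**Step 1: round the article's own paces.**

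| True speed (m/s) | Stored |
|---|---|
| 0.82 to 0.89 (light) | 1 |
| 1.30 to 1.49 (lower moderate) | 1 |
| 1.50 to 1.80 (upper moderate) | 2 |

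The share of the moderate range stored with the light range is (1.5 − 1.3)/(1.8 − 1.3) = 40%; the other 60% is stored as 2. A rise from 0.85 to 1.40 (+0.55) is stored as 1 → 1. A rise from 1.49 to 1.51 (+0.02) is stored as 1 → 2.

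**Step 2: average the rounded bouts.** The analysed value is a per-period average. If bout speeds are normal with mean μ and SD σ, the expected rounded value is Σ k·[Φ((k+0.5−μ)/σ) − Φ((k−0.5−μ)/σ)]. The article gives no σ, so a range is assumed. Apparent rise:

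| True rise | σ 0.05 | 0.10 | 0.15 | 0.20 | 0.30 |
|---|---|---|---|---|---|
| 0.85→1.40 (+0.55) | 0.02 | 0.16 | 0.26 | 0.35 | 0.48 |
| 1.1→1.2 (+0.10) | 0.00 | 0.00 | 0.02 | 0.05 | 0.08 |
| 1.4→1.5 (+0.10) | 0.48 | 0.34 | 0.25 | 0.19 | 0.13 |

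In these examples rounding shrinks the changes that start further below 1.5 m/s and inflates the one that ends there. The bias fades as bout-to-bout spread grows.

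**Step 3: power.** This was simulated with 17 people, 3 periods, 28 bouts per period, between-person SD 0.15, person-by-period SD 0.06 and a linear rise to +0.07 m/s by the third period. All of these except the 17 people and 3 periods are assumptions.

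| Baseline mean (m/s) | Bout SD | Power unrounded | Power rounded |
|---|---|---|---|
| 1.0 | 0.12 | about 0.78 | 0.06 |
| 1.1 | 0.12 | about 0.78 | 0.13 |
| 1.2 | 0.12 | about 0.78 | about 0.29 |
| 1.3 | 0.12 | about 0.78 | 0.49 |
| 1.4 | 0.12 | about 0.78 | 0.59 |
| 1.5 | 0.12 | about 0.78 | 0.62 |
| 1.2 | 0.20 | 0.69 | 0.41 |
| 1.2 | 0.30 | about 0.55 | about 0.40 |

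Rounding lost power in every case tried.

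**Step 4: success scoring, only if it uses rounded speed.** Assume baseline bouts with mean 1.2 and SD 0.15. The share stored as 1 is Φ((1.5−1.2)/0.15) = Φ(2) = 97.7%, with a negligible lower tail. After a true +0.1 shift, the share of bouts above the baseline mean is 1 − Φ((1.2−1.3)/0.15) = 75% unrounded. Rounded, a bout must be stored as 2, so the share is 1 − Φ((1.5−1.3)/0.15) = 9%.

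**Step 5: what recomputation recovers.** For a 250 m bout, the worst-case error from ±0.5 m and ±0.5 s is 250.5/(250/v − 0.5) − v. This is 0.003 m/s at 0.82 and 0.89, 0.006 at 1.3 and 0.010 at 1.8, against up to 0.5 m/s under whole-unit rounding.

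**The case against.** The best defence is that the phrase is a loosely worded unit at the end of a list. The duration item says whole second and the speed item does not say whole. Background quotes paces to one or two decimals, and the Analytic Plan calls speed continuous; both fit badly with a stored scale of 0, 1, 2 and 3. This reading is plausible, so it is not established that the data were in fact rounded. It does not remove the point. The same sentence uses the same construction for resolution twice, the Weather section does so as well, and the reader is given nothing finer.

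It can also be said that feasibility and acceptability are the main focus, and that speed is one of several behavioural measures. That limits the consequence. Speed is still named in the primary aim.

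A reader might infer more than the article supports:

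- **That light and moderate paces become indistinguishable.** They do not; 1.5-1.8 m/s is stored as 2.
- **That the walk-faster outcome is erased.** It is not. Distance and duration are stored, and even averages of rounded bouts keep some signal.
- **That the policy was trained on a rule of crossing 1.5 m/s.** The Architecture section refers to average walking speed per bout and to a comparison with the observation period. It does not say at what precision.
- **That one power figure describes the loss.** The drop to about 0.29 at a mean of 1.2 m/s is one point in a wide range driven by assumptions.
- **That rainfall, recorded as "precipitation to the nearest inch", carries almost no information.** Anything under half an inch would be stored as zero. But the accumulation interval is not stated, and rainfall is one of several context features and not an outcome. It is a side remark only.

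**Conclusion.** The stated resolution is too coarse for a behaviour in the primary aim and conflicts with the article's own pace figures. Step 1 rests on the document alone: all light walking and the lower 40% of the moderate range share one stored value. The bias in period averages and the loss of power are certain in kind if the rule is followed as written. Their size is not, because the article gives no speed SD, number of bouts or expected shift. Under the assumptions above, power falls from about 0.78 to between 0.06 and about 0.6 at a bout SD of 0.12, and from roughly 0.55 to 0.40 at a bout SD of 0.30 and mean 1.2 m/s. The sample size of 17 (20 with attrition) is unaffected. The effect on the success labels is conditional on a step the article does not describe.

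**What to change.** Before analysis:

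1. Compute speed as stored distance divided by stored duration, without rounding, and report it to 0.01 m/s.
2. Use that value in the within-subjects ANOVA or linear mixed model, and in the secondary scoring of walk-faster success.
3. Correct the sentence in Walking and Stationary Behaviors to say so. If the phrase was meant only as the unit, say that.
4. State whether the app's success labels, and hence the trained policies, used rounded or unrounded speed. If rounded, report it as a limitation of the intervention as delivered, because recomputation cannot change prompts already sent.

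The cost is close to nothing. Both inputs are already stored, and the Results section says data collection finished in 2024 with analyses still to be completed. Items 1 and 2 are a single recomputation, item 3 a wording change, and item 4 a check of the app's code.
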